### Assessment and procedures

Assessment and procedures, including those for exploratory objectives (see below) are illustrated in Fig. 1. Briefly, baseline procedures will include: HPV-test, full laboratory tests evaluation, cardiologic assessment including ultrasonography, fiberoscopy and Computed Tomography scan of head, neck, thorax and abdomen. Other tests may be performed at the researcher’s discretion.

**Fig. 1 Fig1:**
[figure not shown]
Schematic timeline of study procedures. Note. History and physical examination, blood count, biochemistry will be repeated weekly during treatment

Each treatment cycle will last 21 days, including administration of cisplatin and CTX on day 1, only CTX repeated on days 8 and 15 and VPA will be given orally throughout the entire cycle. A complete physical exam and a complete serum evaluation of blood cell count, electrolytes, renal and liver function will be performed weekly. Serum concentration of VPA will be assessed every 2 weeks. A complete restaging will be performed after three cycles of chemotherapy and will consist of Computed Tomography scan of head, neck, thorax and abdomen within 21 days from the last chemotherapy administration, a new fibroscopy, a second evaluation of H3 acetylation on blood mononuclear cells peripheral extracted from a peripheral blood sample, a second tumor biopsy in which immunohistochemical assay will be done in order to evaluate marker modification upon treatment. The last one will be performed at the end of treatment (after 3 or 6 cycles) only in presence of measurable and/or evaluable disease.

#### Toxicity evaluation criteria

Acute toxicity will be assessed weekly with clinical examination and blood tests using Common Toxicity Criteria for Adverse Events (CTCAE) of the National Cancer Institute, version 4.0, June 14, 2010.

#### Response evaluation criteria

Response is assessed after 3 cycles. In case of CR, PR, SD, 3 additional cycles will be given. Patients will receive a maximum of 6 cycles. Follow-up tests were carried out every 2 months, until progression.

### Biomarkers

Tumor biopsy and normal mucosa will be collected at baseline (before starting VPA treatment) and possibly within the diagnostic biopsy) at day −2, before starting chemotherapy, and after 3 or 6 cycles of treatment at the first or second evaluation only in presence of measurable and/or evaluable disease. The following markers will be measured: p21/WAF, p16/INK4 and Ki-67/MIB-1, histones and proteins acetylation, as surrogate pharmacodynamic markers of VPA activity on tumor; HDAC isoforms, only at baseline, as potential predictive markers of VPA activity. The tumor expression of all the markers at baseline will be compared with normal mucosa expression and with the tumor expression after treatment. Moreover, at baseline, at day −2 and eventually after 3–6 cycles (see above), EGFR, p-EGFR, MET, RAD51, XRCC1, γH2AX, will be measured as markers of treatment efficacy/resistance evaluated by real-time PCR with the specific primers and probes or by immunohistochemistry. Peripheral blood samples will be collected at baseline, at day −4, 1, 8, at the end of every cycle, at day 22 and at the end of treatment. Histones and proteins acetylation on PBMC will be done as additional surrogate pharmacodynamic markers of VPA activity at different time points during and after treatment. Valproate test will be performed to ensure achievement of the target serum level range and to compare it with histones and proteins acetylation.

Moreover, the CTX induced ADCC activity will be evaluated at baseline by an in vitro assay according to the previoulsy described methods [42] on PBMC and results will be correlated with polymorphisms of FcyRIIa- H131R and the FcyRIIIa-V158F.

### Statistical analysis

The overall response rate (ORR) will be calculated with 95% confidence interval. Time to progression, duration of response and overall survival will be calculated from the first treatment day until the day of event occurrence (for OS the date of death or the date of termination of the trial for patients alive at the time end of the study, or the date of the last follow-up information available for patients lost before the trial end date). Kaplan-Meier methods will be used to estimate all time to event endpoints. For each patient and type of toxicity, the worst degree suffered during the treatment will be described.

Due to the small sample size, statistical analysis of biomarkers data will be conducted with the aim of hypothesis generation. First of all, a complete description of data from biological and pharmacogenomic studies will be done. For biomarkers that might change over time as a consequence of treatment, levels before and after treatment will be compared with appropriate statistical tests, based on the type of data. Serum levels of VPA throughout treatment will be described and compared between different acetylator phenotypes, with appropriate statistical tests. *P* values ≤0.05 will be considered significant, and no adjustment is planned for multiple comparisons due to the exploratory nature of the analysis.

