**Method/Design:**

V-CHANCE is a phase 2 clinical trial evaluating, in patients with recurrent/metastatic squamous cell carcinoma of the head and neck never treated with first-line chemotherapy, the concomitant standard administration of cisplatin (on day 1, every 3 weeks) and cetuximab (on day 1, weekly), in combination with oral VPA given daily from day −14 with a titration strategy in each patient (target serum level of 50–100 μg/ml). Primary end point is the objective response rate measured according to Response Evaluation Criteria in Solid Tumors (RECIST). Sample size, calculated according to Simon 2 stage minimax design will include 21 patients in the first stage with upper limit for rejection being 8 responses, and 39 patients in the second stage, with upper limit for rejection being 18 responses. Secondary endpoints are time to progression, duration of response, overall survival, safety.

Objectives of the translational study are the evaluation on tumor samples of markers of treatment efficacy/resistance (i.e. γH2AX, p21/WAF, RAD51, XRCC1, EGFR, p-EGFR, Ki-67) and specific markers of VPA HDAC inhibitory activity (histones and proteins acetylation, Histone deacetylase isoforms) as well as valproate test, histones and proteins acetylation of peripheral blood mononuclear cell, tested on blood samples at baseline and at different time points during treatment.

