### Study design

V-CHANCE is a phase 2 study performed in patients with recurrent/metastatic SCCHN never treated with first-line chemotherapy. Patients will be treated with cisplatin (75 mg/m^2^ on day 1 to be repeated every 21 days), CTX (loading dose of 400 mg/m^2^ followed by a maintenance dose of 250 mg/m^2^ to be repeated weekly) and VPA (increasing oral doses, from 500 mg/day on day −14 until a full dose of 1500 mg at day 1, with a titration strategy in a patient for a target serum level range of 50–100 μg/ml). RECIST criteria version 1.1 will be employed with the aim to determine the response rate. In particular, complete responses (CR) will be defined as the total disappearance of all target lesions; partial response (PR) will be observed when the sum of largest diameters of the target lesions will decrease by at least 30%. A 20% increase in the sum of diameter of target lesions will qualify as progressive disease (PD). Stable disease will be defined as neither sufficient shrinkage to qualify for PR nor sufficient increase to qualify for PD. Overall response rate (ORR) will be calculated as the sum of CRs and PRs; while disease control rate (DCR) will correspond to the sum of PS, CRs and SDs).

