### Treatment plan

Treatment with VPA includes a titration strategy applied in each patient looking for a serum concentration that is considered useful to produce the desired synergistic effect with cisplatin and CTX. Treatment will be administrated orally starting at day −14 with a 500 mg slow releasing tablet at evening. Thereafter, the dose will be increased also using 300 mg tablets (Table 1).

**Table 1 Tab1:** Valproic acid dose titration

Days	Morning dose (mg)	Afternoon dose (mg)	Evening dose (mg)
−14 and −13	0	0	500
−12 and −11	300	0	500
−10 and −9	500	0	500
−8 and −7	500	300	500
−6 and −5	500	500	500
−4 and −3	500	500	500
−2 and −1	500	500	500

The interval between each dose will be 12 h from the −14 day to −9 day and it will be 8 h from −8 day

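### Duration of response is counted from the first treatment day, so it includes the weeks before any response can be documented

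*Protocol article*

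**What the plan says.** The Statistical analysis section sets one rule for three endpoints: "Time to progression, duration of response and overall survival will be calculated from the first treatment day until the day of event occurrence". It adds that "Kaplan-Meier methods will be used to estimate all time to event endpoints". It spells out the end date only for overall survival; for the other two the end is simply the event.

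The Abstract lists duration of response as an endpoint distinct from time to progression: "Secondary endpoints are time to progression, duration of response, overall survival, safety". The Objectives section does the same.

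The schedule is given elsewhere in Methods/Design:
- Response evaluation criteria: "Response is assessed after 3 cycles".
- Assessment and procedures: "Each treatment cycle will last 21 days, including administration of cisplatin and CTX on day 1". The restaging CT is to be done "within 21 days from the last chemotherapy administration".
- Treatment plan, on valproic acid (VPA): "Treatment will be administrated orally starting at day −14 with a 500 mg slow releasing tablet at evening". Cisplatin and cetuximab start on day 1.

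The Study design section states that "RECIST criteria version 1.1 will be employed with the aim to determine the response rate" and describes CR and PR as disappearance or shrinkage of target lesions. Nothing in the article starts duration of response at the first documented CR or PR.

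**The concern.** CR and PR are changes relative to baseline, so no patient can be in response on the first treatment day. A duration that starts there measures the time on study before response plus the time in response. To be counted as a responder at all, a patient must have reached an assessment without progressing, so the first part of the interval is guaranteed by the selection of responders and says nothing about how long responses last.

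The separate endpoint is also at risk of being empty. With the same origin, and with progression as the end of both, duration of response is just time to progression restricted to responders.

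The article describes one regimen tested with a Simon two-stage rule and no comparator arm. Readers will therefore set the reported durability beside outside results. A figure that includes pre-response time favours the regimen and cannot be compared with durations counted from response.

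**Working it through.** The article states no figure for duration of response, so there is none to reproduce. The check is calendar arithmetic on its own schedule.

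**Inputs**
- Cycle length 21 days (Assessment and procedures).
- First response assessment after 3 cycles; at most 6 cycles (Response evaluation criteria).
- CT within 21 days of the last chemotherapy administration (Assessment and procedures).
- First VPA dose on day −14 (Treatment plan). Table 1 runs to day −1 and chemotherapy starts on day 1, so with no day 0 the lead-in is 14 days.

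**Formula**

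Overstatement per responder = date of first documented response − first treatment day.

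**1. Nominal schedule, response seen at the first restaging**
- From day 1: 3 × 21 = 63 days = 9 weeks.
- From day −14: 63 + 14 = 77 days = 11 weeks.

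**2. Allowing for the CT window**
- The cycle 3 cisplatin dose falls 2 × 21 = 42 days after day 1. A scan within 21 days of it falls between 42 and 63 days, that is 6 to 9 weeks from day 1, or 8 to 11 weeks from day −14.
- If the last chemotherapy administration is instead taken as cetuximab on day 15 of cycle 3, the start is 42 + 14 = 56 days. The scan then falls between 56 and 77 days, that is 8 to 11 weeks from day 1, or 10 to 13 weeks from day −14.

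**3. Response first documented after cycle 6**
- From day 1: 6 × 21 = 126 days = 18 weeks.
- From day −14: 126 + 14 = 140 days = 20 weeks.

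**4. Illustration for one responder**

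The progression times are assumed, since the article gives none. Time runs from day 1, and both clocks stop at progression.

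| Progression, weeks from day 1 (duration as planned) | Counted from response at week 9 | Planned value too long by | Counted from response at week 6 | Planned value too long by |
|---|---|---|---|---|
| 26 | 26 − 9 = 17 | 9/17 = 53% | 26 − 6 = 20 | 6/20 = 30% |
| 39 | 39 − 9 = 30 | 9/30 = 30% | 39 − 6 = 33 | 6/33 = 18% |
| 52 | 52 − 9 = 43 | 9/43 = 21% | 52 − 6 = 46 | 6/46 = 13% |

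In every row the planned duration of response equals the time to progression. The relative error is largest when responses are short.

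**The case against.** The strongest reply is about weight. Duration of response is one of several secondary endpoints, and no hypothesis, threshold or decision rests on it. The decision rule uses response counts only (8 of 21, then 18 of 39), and the primary endpoint is the objective response rate. Neither changes. The scan dates will exist, so the duration can be recalculated at analysis. All of this stands and limits how serious the point is. It does not defend the definition, which the article states outright and so does not leave to a fuller document.

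Four stronger readings are tempting, and the article does not support them.

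- **At least nine weeks.** A reader might take nine weeks as a minimum. It is the nominal value; the CT window can be read to allow a scan from week 6.
- **A fixed amount for everyone.** The excess depends on when response is first documented. A patient with stable disease after cycle 3 continues treatment and may respond later, with an excess of 18 to 20 weeks. Adding one constant to a median therefore assumes that every response appears at the first scan.
- **Always identical to time to progression.** This holds only if both endpoints end at the same event. The text does not say how deaths without progression are handled.
- **Patients lost in the VPA lead-in are excluded.** A time origin is not a rule about who is analysed, and the article states no such exclusion.

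On the origin itself, the article calls VPA dosing treatment and starts it on day −14, which favours that reading. Cycles, however, are numbered from day 1. The wording is open to both readings, but the effect on time to progression and overall survival is only 14 days.

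**Conclusion.** The definition of duration of response is wrong as written and biases a listed secondary endpoint upward. For a response seen at the first restaging, the excess is about 9 weeks from day 1 on the nominal schedule, or roughly 6 to 9 weeks with the CT window counted from the cycle 3 cisplatin dose. A day −14 origin adds two weeks. For a response first documented after cycle 6, the excess is about 18 weeks from day 1 or 20 from day −14.

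These sizes rest on the planned visit schedule. The percentages in the illustration also rest on assumed progression times and are not estimates for this trial. The equality with time to progression is conditional on a common end event.

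This should be corrected before the endpoint is analysed. It does not threaten the trial's main conclusion, because the response rate and the Simon rule do not use it. The day −14 or day 1 question is a minor clarification.

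**What to change.** Take duration of response out of the shared sentence in the Statistical analysis section and define it separately: in patients with CR or PR only, the time from the first assessment documenting CR or PR to progression or death, estimated by Kaplan-Meier.

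For time to progression and overall survival, state whether the first treatment day is the first VPA dose (day −14) or day 1, and use that one origin for all patients.

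The cost is one or two sentences. No extra patients, visits or data are needed, because the assessment dates are already collected to determine response. The reported durations will be shorter, and duration of response will then carry information that time to progression does not.

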### Biomarkers study

SCCHN, given the relative accessibility of tumor to sample, is an ideal cancer type to assess the efficacy of new therapeutic approach with biopsy samples taken before and during treatment to identify biomarkers of response and resistance.

VPA serum levels was correlated in several studies with histone acetylation in tumor samples and in PBMC and was also linked to baseline expression of HDAC isoforms. In oral tongue cancer (generally HPV-negative) it has been demonstrated that HDAC1 and 2 are overexpressed and associated with significantly shorter progression-free survival (PFS) [30]. Moreover, in several clinical studies the measurement of histone acetylation on PBMC has been studied as a surrogate marker of HDACi activity; however, in most cases this measurement has not been successfully linked to clinical outcome. Recently Yardley et al., have analyzed protein lysine acetylation in pre- and post-treatment samples collected in a subset of 49 breast cancer patients treated with the combination of the HDACi entinostat plus exemestane demonstrating that hyperacetylation of protein lysines in PBMC was associated with improved clinical outcome, as shown by the prolonged PFS in hyperacetylators versus low acetylators [31]. Elevated levels of protein lysine acetylation maintained in certain patients despite entinostat levels at or below the level of detection at the time of sampling seem to reflect the durability and potency of the pharmacodynamic effects that low sustained concentrations of entinostat can elicit. Biomarker studies in clinical trials have shown that, besides histone hyperacetylation, the major effects of HDAC treatment in solid tumors were p21 overexpression and Ki-67/MIB-1 downregulation, two features typically related with cell differentiation and growth arrest. As mentioned above, HDAC inhibitor can sensitize cancer cells to cisplatin by different mechanisms including the regulation of the expression of DNA repair genes such as RAD51 [32] and the downregulation of antiapoptotic genes such as BCL2 and XIAP [8]. There are evidences that cancer with moderate expression of EGFR are more sensitive to CTX compared with those that express very high levels of EGFR [33]. Preclinical study showed CTX resistant cell line express not only increase in EGFR but in also other members of the same family and in particular HER2 and HER3 as well as MET. HER4 has been observed overexpressed in some HNSCC cancer cell lines where it is associated with higher proliferative rate [34]. It has been observed that MET expression represent an independent predictor of reduced disease-free and overall survival in HNSCC patients [35]. Even more compelling are data that correlate MET expression and radiation [35], cisplatin [36, 37] and CTX [38] in SCCHN. The majority of SCCHN (>90%) overexpress the epidermal growth factor receptor (EGFR or HER1) HER1, which correlates with a poor prognosis and overall resistance to therapy. Immunotherapy with the EGFR-specific IgG1 mAb, CTX, significantly improves survival of SCCHN patients with advanced or metastatic disease [25]. The available evidence is consistent with the possibility that the beneficial effects of CTX administration on the clinical course of the disease reflect both inhibition of EGFR tyrosine phosphorylation and triggering of antibody-dependent, cell-mediated cytotoxicity (ADCC) of SCCHN cells [39]. Binding of CTX to the EGFR leads to internalization and degradation of the antibody–receptor complex and down-regulation of EGFR expression [33]. Also CTX can activate immune cells that bear receptors for the Fc (constant portion) of IgG such as natural killer (NK) cells. NK cells have an activating Fc receptor for IgG (FcγRIIIa), which mediates Ab dependent cellular cytotoxicity (ADCC) and enhances production of interferon-γ (IFN-γ) in response to Ab-coated targets [40, 41]. We previously demonstrated that FcγRIIIa polymorphisms were significantly associated with response to anti-EGFR-based therapy in 49 colorectal cancer patients with KRAS wt tumors, The results suggested that prognosis is particularly unfavorable for patients carrying the FcγRIIIa-158F/F genotype [42].

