### Objectives

The primary objective of the study is to assess whether VPA, given concomitantly with the conventional cisplatin-cetuximab regimen, can improve treatment activity (in terms of objective response rate) in patients with recurrent/metastatic SCCHN.

Secondary objectives are response duration, time to progression, overall survival, safety.

A translational study is also planned with several objectives: (a) to compare the expression of several biomarkers (p21/WAF, p16/INK4 and Ki-67/MIB-1, histones and proteins acetylation (H&P-Ac), HDAC isoforms) in the tumor and normal mucosa, to evaluate the tumor expression of markers of treatment efficacy/resistance (pEGFR, MET, RAD51, XRCC1, Bcl2 and XIAP γH2AX, VEGF). (b) to evaluate Histones and proteins acetylation on PBMC as additional surrogate pharmacodynamic markers of VPA activity at different time points during and after treatment. (c) to ensure achievement of the target serum level range, performing valproate test, and to compare it with histones and proteins acetylation.

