In the morning of day −4, within 2 h after taking the morning dose, serum level of VPA will be checked using a commercially available valproate test, and will be adjusted depending on the reached steady level. The target serum level range will be 50–100 μg/ml which represents the recommended values for the treatment of epilepsy. At any time, in case of grade 2 somnolence or fatigue the VPA dose will be reduced by 200 mg/day steps up to reaching grade ≤1 independently of the actual serum level. In case of grade ≥3 somnolence or fatigue VPA will be definitely discontinued. In case of asymptomatic QTc prolongation development (QTc >500 ms, or QT prolongation >600 ms,) VPA has to be interrupted. Electrolytes and concomitant medications have to be checked and corrected. ECG has to be repeated after 24 h. If the event is resolved, treatment with VPA can be resumed but the dose will be reduced by −200 mg/day; on the contrary, if QT prolongation is confirmed VPA has to be interrupted [43, 44]. In case of symptomatic QTc prolongation development (QTc > 500 ms or QT prolongation > 600 ms,) and association with symptoms suggestive of a ventricular tachyarrhythmia, VPA has to be interrupted. At day 1 cisplatin at dose of 75 mg/m2 given every 3 weeks and CTX at induction dose of 400 mg/m2 followed by maintenance doses of 250 mg/m2 given weekly, will be administered. Adequate intravenous hydration will be required prior and after cisplatin administration. Antiemetic prophylaxis with dexamethasone and palonosetron before cisplatin will be also administered. Toxicity due to cisplatin administration may be managed by symptomatic treatment, dose interruptions and dose adjustment. Once the dose has been reduced it should not be increased at a later time. Doses of cisplatin omitted for toxicity are not replaced or restored. At the time of recycling, blood tests have to be normal (Absolute Neutrophil Count 1.5 × 10^9^/L, platelets 100 × 10^9^/L). If lower values, or at least grade 2 non-hematologic toxicities, are detected, treatment will be interrupted and restored when toxicity is back to grade 1, treatment will be restarted at the same drug dosage. If at any time during a chemotherapy cycle febrile neutropenia, grade 4 neutropenia, grade 4 thrombocytopenia, non-hematologic grade 3 toxicities occur, the subsequent chemotherapy doses will be administered with 50% of the initial dose. No primary prophylaxis with G-CSF is allowed, but secondary prophylaxis is allowed.

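### Comparing serum VPA between acetylator phenotypes groups a measured marker and discards information; acetylation should be analysed as a continuous outcome on VPA level

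*Protocol article*

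**What the plan says.** The Statistical analysis section names one analysis that links drug level to acetylation: "Serum levels of VPA throughout treatment will be described and compared between different acetylator phenotypes". Acetylation is the grouping factor and serum VPA the variable compared.

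The aim is worded more openly elsewhere. Objective (c) is "to ensure achievement of the target serum level range, performing valproate test, and to compare it with histones and proteins acetylation", and the Biomarkers section says much the same. Neither mentions groups. The Biomarkers section also fixes the role of acetylation: "Histones and proteins acetylation on PBMC will be done as additional surrogate pharmacodynamic markers of VPA activity at different time points during and after treatment". Under Treatment plan, VPA is titrated: "The target serum level range will be 50–100 μg/ml", with adjustment after a level taken on day −4.

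The article gives no number of phenotypes and no cut-point. The nearest wording is in the background (Biomarkers study), on a breast cancer study of another HDAC inhibitor: "prolonged PFS in hyperacetylators versus low acetylators". That contrast related the groups to outcome, not to drug level.

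Biomarker analyses are declared hypothesis-generating, with P ≤0.05 called significant and no multiplicity adjustment.

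**The concern.** Acetylation is an assay measurement, and the question is how it relates to VPA level. Sorting patients into phenotypes replaces the measurement with a category and treats everyone within a category as alike. In a trial of at most 39 patients, that discards information the assays have already supplied.

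The orientation also matters for reading the result. Acetylation is the effect marker and VPA is the exposure, yet the planned output is a difference in VPA between groups. That does not say how much acetylation changes per unit of VPA, which is the quantity one would want when judging a target range.

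At stake is an exploratory result. A non-significant group comparison, judged at 0.05 in a small sample, could be taken as evidence that acetylation is unrelated to level when the method was simply insensitive.

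**Working it through.** **Inputs from the Protocol article.** Maximum sample size 39 and first stage 21 (Sample size calculation); significance at P ≤0.05 (Statistical analysis).

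**Assumptions, because the article gives no figure.** Phenotypes are cuts of measured acetylation; bivariate normality; one VPA–acetylation pair per patient; all patients evaluable; two-sided test; true correlation of 0.3 to 0.5. The article states no power or precision for this analysis, so there is no planned figure to reproduce.

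**1. Information kept after grouping one variable.** For two groups with a fraction q below the cut c = Φ⁻¹(q), the share kept is φ(c)² / [q(1 − q)].

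- Median split: φ(0)² / 0.25 = 0.1592 / 0.25 = 0.637 (= 2/π), a loss of 36.3%.
- 25/75: 0.3178² / 0.1875 = 0.539, a loss of 46.1%.
- 10/90: 0.1755² / 0.09 = 0.342, a loss of 65.8%.

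For k groups, the share kept is the between-group variance of the grouped standard normal, Σ pⱼmⱼ².

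- Tertiles: group means −1.091, 0, 1.091, so (2/3) × 1.091² = 0.793, a loss of 20.7%.
- Quartiles: group means ±1.271 and ±0.325, so 0.5 × (1.271² + 0.325²) = 0.861, a loss of 13.9%.

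| Grouping | Kept | Lost | 39 patients act like |
|---|---|---|---|
| Quartiles | 0.861 | 14% | 33.6 |
| Tertiles | 0.793 | 21% | 30.9 |
| Median split | 0.637 | 36% | 24.8 |
| Two groups, 25/75 | 0.539 | 46% | 21.0 |
| Two groups, 10/90 | 0.342 | 66% | 13.3 |

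**2. Power.** Simulation with 3,000 runs per setting, two-sided 0.05:

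| N | Correlation | Continuous (Pearson) | Median split (t test) | Tertiles (F test) |
|---|---|---|---|---|
| 39 | 0.3 | 45% | 31% | 28% |
| 39 | 0.4 | 74% | 52% | 51% |
| 39 | 0.5 | 92% | 76% | 75% |
| 21 | 0.4 | 46% | 31% | 27% |

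As a check on the continuous column at N = 39 and correlation 0.4, the Fisher z approximation gives Φ(0.4236 × √36 − 1.96) = Φ(0.58) = 72%, close to the simulated 74%. Tertiles keep more information than a median split, but an overall F test spends two degrees of freedom and gives the gain back.

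**3. Does making VPA the compared variable cost information?** The slope test depends only on the correlation, t = r√[(n − 2)/(1 − r²)], which is the same in both directions. In one simulated sample of 39 the slope P value was 0.00519 both ways. The whole loss in steps 1 and 2 comes from grouping.

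**The case against.** The strongest reply is that this is exploratory detail in a condensed article. The definition of the phenotypes and the handling of repeated levels may sit in a full protocol or analysis plan that is not shown, and no power is claimed. That stands as to weight: the absence of a cut-point is not the finding. The article does, however, commit to a between-group comparison, and that stated choice is what can be improved.

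Four stronger readings are tempting and are not supported.

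- A reader might infer that about a third of the information is lost. That figure holds only for two groups cut at the median. The article fixes no grouping, so only the range can be given.
- A reader might infer that the analysis reverses the stated objective. Objective (c) and the Biomarkers section give no direction, and they do not exclude a continuous analysis.
- A reader might infer that this is the trial's only test of whether VPA has its intended effect. The same section plans a comparison of biomarker levels before and after treatment, which is a more direct test.
- A reader might infer that both quantities are measured in the same sample at every visit. The Biomarkers section lists blood-sampling days without assigning both assays to each, while Assessment and procedures has VPA levels every 2 weeks and a second H3 acetylation evaluation at restaging after three cycles.

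It is also fair to say that titration to a target narrows the VPA range and so weakens a slope as well. That stands: no choice of analysis restores variation that titration removes.

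**Conclusion.** The point holds as a low-priority improvement to an exploratory analysis. Grouping a measured pharmacodynamic marker loses between about 14% and 66% of the information on its association with VPA level, depending on a grouping that the article does not fix. At an assumed correlation of 0.4 and 39 patients, a median split takes power from about 74% to 52%. These figures rest on bivariate normality, one pair per patient and full evaluability; the correlation is an assumption, not a trial figure. Placing VPA in the response position costs no information but gives a less useful estimate. The primary and secondary endpoints are unaffected.

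**What to change.** For objective (c), make the main exploratory analysis a model with acetylation as a continuous outcome (change from baseline, suitably transformed) and VPA level as the predictor. Use the time points at which both were measured, and add a patient random effect where patients contribute repeated pairs. Report the slope with its confidence interval. Keep the comparison of VPA between phenotypes as a descriptive table.

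The cost is essentially a change of wording, since no new samples or assays are called for. There are two small downsides: a transformation has to be chosen, and the analysis is restricted to time-matched samples, which may be fewer than the blood-sampling days suggest. The text should acknowledge that titration to 50–100 μg/ml may limit the precision of the slope, so that a wide interval is not read as absence of a relation.
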